### Participants

Participants will be children referred to the child and adolescent mental health department at Sorlandet Hospital (Abup) in Southern Norway. As a standard procedure at the clinic, regardless of whether one takes part in a research project, all clients (i.e., children) undergo a standardized assessment of their functioning and symptoms of mental distress and developmental history. If, from the initial assessments, it is determined that the client is eligible for a family-based treatment in the family team of the clinic, the children and their parents will be invited to take part in this study. To be eligible, the following criteria must be met: a) the child meets the criteria for a mental health disorder, b) the disorder is assessed by health professionals to be related to parent or family functioning, and c) the families are motivated to work within a family-based framework to improve the suffering of their child and the relational difficulties in the family. The main researcher or the head of the family team will provide participants information about the study in age appropriate ways and go through the written consent form. After consent for participation, each family (one child with one or two parents) will be assigned randomly to one of the treatment conditions using the www.randomizer.org website. Randomization will be requested by the therapist responsible for recruitment and clinical interviews. Based on the clinic’s experience of research, an anticipated drop-out rate of 20% is reasonable [35, 36]. With 80% power, an expected effect size of 0.4, and an anticipated 20% drop-out rate, the number of clients in each condition is calculated to be 60, following a procedure described by Schönbrodt & Wagenmakers [37]. By choosing Bayesian statistics, evidence will be obtained even when the power calculations might be mis specified [38].

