### Data analyses

To test our first hypothesis that the two conditions are equivalent when it comes to effectiveness, Bayesian growth curve analysis and t-tests will be used to assess the effect of the two arms as compared to each other. Independent sample t-test will be performed on the SDQ to compare the outcome of the two conditions for every five clients included in the study. If strong evidence of difference of the treatment effect is provided with few clients, the data collection can stop. To test our second hypothesis that an increase in parents’ emotional functioning predicts a decrease in mental health symptoms for their children, Bayesian growth curve analyses will be used. Bayesian analysis is preferred because it allows for the specification of models that are appropriate for the data and the capacity to provide estimates and credible intervals for any derived parameter. Additionally, when using Bayesian analysis, credible intervals are not dependent on large-N approximations (as confidence intervals used in frequentist statistical approaches), nor are credible intervals dependent on the type of test being performed (as confidence intervals do in frequentist approaches). Furthermore, Bayesian analysis gives methods for evaluating support for the null hypothesis, not just against it [66]. Moreover, it enables monitoring of data collection to see whether there is sufficient evidence to draw conclusions or if additional data is required [67]. Indeed, there is evidence that within child and adolescent mental health research, conclusions could have been made with smaller sample sizes than what was obtained in many cases [68]. The effect size of interest is the difference in treatment effect between each of the arms in the study. Effect sizes of treatments within our field vary [10, 69], with treatment effects of 0.80 regarded as good. In line with conventional procedures in meta-analyses [65], we consider a difference of 0.40 as meaningful. Based on the experience of research within the clinic, an anticipated drop-out rate of 20% is reasonable [35, 36]. Clinical significant change will be assessed using the method defined by Jacobson & Truax [54]. Missing data will be managed with multiple imputation and all analyses will be performed as intention to treat (ITT).

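### The stated inputs for the between-arm t-test do not reproduce 80% power at an effect size of 0.4 with 60 per condition and 20% drop-out

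*Protocol article*

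**What the plan says.** The Participants section gives inputs and a result for a stated power of 80%: "an expected effect size of 0.4, and an anticipated 20% drop-out rate, the number of clients in each condition is calculated to be 60". It attributes this to a cited procedure that the article does not describe. It then adds that Bayesian statistics will yield evidence even if the power calculation turns out to be wrong.

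The Data analyses section says what the effect size refers to: "The effect size of interest is the difference in treatment effect between each of the arms in the study", and "we consider a difference of 0.40 as meaningful". It also names a between-arm test: "Independent sample t-test will be performed on the SDQ to compare the outcome of the two conditions", repeated after every five clients, with the option to stop early if strong evidence of a difference appears. Bayesian growth curve analysis is listed beside the t-tests for the same hypothesis.

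The article states no alpha, sidedness, Bayes-factor threshold, prior or correlation between SDQ time points.

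**The concern.** The article prints both the inputs and the output of a sample-size calculation, so a reader can repeat it. For a two-group comparison at a standardised difference of 0.4, about 50 evaluable per arm is roughly half of what 80% power usually needs.

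The figure matters because the first hypothesis is that the two treatments are equivalent. The Discussion says that EFST should go to more families if it proves as beneficial as TAU. A reader who takes the 80% at face value may give a null or inconclusive SDQ comparison more weight than it deserves.

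**Working it through.** **Inputs from the article.** Effect size d = 0.4 (Participants; Data analyses), defined as a between-arm difference (Data analyses). Enrolment is 60 per condition and drop-out 20% (Participants), so 60 × 0.8 = 48 evaluable per arm. The test is an independent-samples t-test (Data analyses).

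**Inputs assumed.** Alpha 5%, two-sided or one-sided. For Bayes factors: thresholds of 3 and 10, and either a default Cauchy prior (scale 0.707) or informed priors centred at 0.35 to 0.4.

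**1. Trying to reproduce 60.** Per arm, n = 2(z₁₋α + z₀.₈)²/d², with α/2 in place of α for a two-sided test.
- Two-sided 5%: 2 × (1.960 + 0.842)²/0.16 = 98.1. The exact noncentral t gives 99.1, so 100 evaluable and 100/0.8 = 125 enrolled.
- One-sided 5%: 2 × (1.645 + 0.842)²/0.16 = 77.3. The exact value is 78, and 78/0.8 = 97.5, so 98 enrolled.
- One-sided 10%: about 72 enrolled.

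None of these gives 60. A paired or one-sample formula at 0.4 needs about 50, which becomes 50 × 1.2 = 60 or 50/0.8 = 62.5 after allowing for drop-out. That answers a within-arm question, not the between-arm one that the article defines. Whether it is the source of the 60 cannot be told from the article.

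**2. Power at the stated size.** The noncentrality is d√(n/2). With n = 48 it is 0.4 × √24 = 1.96 on 94 degrees of freedom.

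| Evaluable per arm | Two-sided 5% | One-sided 5% | One-sided 10% |
|---|---|---|---|
| 48 | 49% | 62% | 75% |
| 60 (no drop-out) | 58% | 70% | 82% |

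The only entry above 80% needs a one-sided 10% level and no drop-out, which discards the article's own 20%. The difference detectable with 80% power (two-sided 5%) is 0.58 with 48 per arm and 0.52 with 60.

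**3. Reading power as the chance of a Bayes factor above a threshold** (true d = 0.4, 48 per arm).
- Default two-sided Cauchy prior, fixed n: the critical t is 2.46 for a factor of 3 and 2.99 for 10. The chances of exceeding them are 31% and 16%.
- Same prior, sequential looks: 41% and 23%.
- Informed priors, sequential looks, stopping for either conclusion: about 72% to 75% for a factor above 3, and about 46% to 52% for a factor above 10.

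**4. Reading power as that of a baseline-adjusted or longitudinal analysis.**
- Adjusting one follow-up for baseline multiplies the variance by 1 − r². Reaching 80% with 48 per arm needs r = √(1 − (0.4/0.578)²) = 0.72.
- For the baseline-adjusted mean of the three SDQ follow-ups (T1 to T3), with equal correlations r, the variance factor is (1 + 2r)/3 − r². Its maximum, at r = 1/3, is 5/9 − 1/9 = 0.444. The effective difference is then at least 0.4/√0.444 = 0.60, and power is at least 83% (two-sided 5%). With correlations that decay over time, power is about 81% to 88%. All of this assumes a constant 0.4 effect and complete follow-up in the 48.

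**The case against.** The strongest reply is that 49% belongs to an assumed test. The article adopts no p-value rule, specifies Bayesian analysis throughout, and takes its 60 from a cited procedure whose settings may be in the fuller protocol. This stands as far as it goes. A reader might infer that the design simply has 49% power, or a coin-flip chance, and the article does not support that without conditions.

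A reader might also infer that a Bayes-factor criterion always does worse than the t-test, or that no analysis could reach 80%. Neither holds. Informed priors with sequential looks do better than 49% for a factor above 3. Stopping only for a difference, with denser looks, raises the chance to about 75% to 79% at 48 per arm. In a check with looks every five clients it touched 80% in one limiting case, where the prior is a single point at exactly the true 0.4. With 60 evaluable and no drop-out, such designs can pass 80%. The longitudinal analysis in step 4 can also exceed 80%, and growth curve analysis is one of the planned methods.

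These points do not rescue the printed statement. The Participants section invokes no longitudinal model or correlation, and no informed prior or lenient threshold. The remark about mis-specified power concerns whether the evidence can be interpreted. It does not make 80% correct.

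Finally, a reader might infer that the trial will treat a null result as ruling out 0.4 because of its claimed power. The article does not say so. It says that Bayesian methods can weigh support for the null directly.

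**Conclusion.** The point holds in conditional form. For the between-arm t-test that the article names, 60 per condition with 20% drop-out does not give 80% power at 0.4. The shortfall is about a factor of two in sample size on a two-sided 5% basis (48 evaluable against 100) and still large one-sided (48 against 78).

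On a Bayes-factor criterion with stopping for either conclusion, none of the priors and thresholds tried reaches 80% at 48 per arm. The t-test figures rest on the assumed alpha and sidedness, and the Bayes-factor figures on the assumed prior, threshold and looks. The conclusion that the stated inputs do not produce 60 holds for every two-group t-test variant tried with the article's own drop-out.

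**What to change.** Keep 120 families. In the Participants section, replace the bare 80% with the figure that the chosen criterion delivers at 48 evaluable per arm, on one of three bases:

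- **Bayes factor:** give the threshold, prior, sidedness and look schedule, with the simulated probability of reaching the threshold at 0.4.
- **t-test:** give the alpha and the resulting power. For two-sided 5% this is about 49% at 0.4, with a detectable effect of about 0.58.
- **Growth model:** give the assumed correlations and follow-up, and the power that they produce.

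In reports, do not describe a null or inconclusive SDQ result as coming from a trial with 80% power at 0.4, unless the restated calculation supports it.

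The cost is a change of wording and one short calculation or simulation. On the first two bases, the stated power will probably become less favourable.

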### Inclusion and exclusion criteria

As EFST is a transdiagnostic intervention, children with a wide range of clinical diagnoses (such as a variety of anxiety disorders and depression) as measured by K-SADS will be included. Children 6–18 years of age will be invited to participate in the project, and it is preferred that both parents participate in the EFST treatment (however, the family/or child can still be included if only one parent is able to participate). To be eligible for the study, parents must reside with their child and speak Norwegian well enough to understand and participate in sessions without an interpreter. Lastly, the child should not be receiving other psychotherapy at the clinic while in the trial.

### Retention

The main researcher of the trial will contact all parents included in the trial by telephone to ensure adequate information regarding the interventions, appointments and dates. Participants will also receive electronic links with reminders to respond to questionnaires.

### Research conditions

#### Condition 1: EFST Intervention

This condition consists of a parental EFST group-based workshop followed by 6 individual sessions. The workshop is conducted over two days, lasting a total of 13 h. Each group consists of 6–16 parents, ideally both parents of a referred child. In contrast to TAU, in this condition, the child does not participate in the treatment; only their parents do. The overall goal of EFST is to increase parents’ emotional competence and help parents work through their respective emotional barriers, such as fear and shame, that may prevent their effective parenting [12]. The manualized workshop utilizes psychoeducation experiential exercises and specific skills training. Two therapists conduct the workshop together. Individual supervision sessions will continue the process begun during the two-day workshop and will adhere to the EFST treatment manual [12]. EFST supports parents to follow their intention to engage actively in their child’s recovery process by increasing parental self-efficacy, emotional competence, and their ability to repair and strengthen the relationship with the child. Four core parenting skills are taught in the workshops and then elaborated and worked on in the individual sessions. The four core skills include:1. *Validation of emotion*. Instead of trying to problem-solve or remove the child’s symptoms, parents are trained to recognize, understand, and communicate emotional understanding to their child. Being validated by parents when experiencing painful emotions has the potential to help children better understand and regulate their emotions [12].2. *Enhancing motivation*. Parents are helped to understand and experience how their own problematic emotions, such as maladaptive shame and fear, can disrupt the parent–child interaction and prevent them from providing emotional guidance to their children.3. *Resolving interpersonal injuries*. Parents are guided to take responsibility for ruptures in the relationship and repair past emotional injuries to strengthen the emotional bond with the child.4. *Setting boundaries*. Building on the previous core skills, parents are helped to set healthy and flexible boundaries without judgment.

Guiding values for the therapist are the humanistic principles of empathy, unconditional positive regard, and genuineness [12, 39]. In the EFST individual sessions, evocative techniques (i.e., imaginative two-chair dialogues) are used as a central part of the intervention to help parents facilitate and engage in deeper emotional processing [12]. The parents will receive 19 h of EFST (13 h in group and 6 h of individual sessions). All EFST individual parent sessions will be videotaped to ensure adherence and provide data for a connected study that will further investigate the active mechanisms of change that may be at play in this intervention.

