EFST is an increasingly used treatment approach among therapists in outpatient clinics for child and adolescent mental health (i.e., BUP) in Norway. One example is the Department of Child and Adolescent Mental Health at Sorlandet Hospital (Abup) in Southern Norway, which has offered EFST to more than one hundred families during 2021. Prior studies examining the effects of EFST in community settings have demonstrated promising results, both when provided as a two-day caregiver workshop [21–23] and as a two-day workshop followed by individual sessions [24]. In a previous trial conducted by researchers affiliated with this current trial, two versions of EFST were compared in a randomized clinical dismantling study. Participants were parents of children with mental distress in a community sample. The standardized EFST protocol was compared to a psychoeducational version of EFST [24]. Results showed a significant decrease in both internalizing and externalizing symptoms, and the standard EFST protocol produced the most promising results. A weakness of the study was the absence of a comparison group other than the two EFST treatment variants. Thus, a comparison of EFST to a waitlist or active control group is necessary to determine its effectiveness.

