### Therapists

Therapists in the TAU condition are all qualified mental health professionals employed at the clinic’s family team. The team (*N* = 12) consists of certified family therapists, psychologists, and one psychiatrist.

Five qualified EFST therapists employed on the family team (three family therapists and two psychologists) will conduct the EFST intervention. During the data collection, the EFST therapists will gather monthly for three-hour supervision sessions to discuss video material, dilemmas, technical and ethical considerations, and ensure treatment fidelity.

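### The SDQ t-test that compares the arms and drives stopping treats EFST families as independent, although they share workshops and five therapists

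*Protocol article*

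**What the plan says.** Under Participants, each family is randomised on its own, with one child and one or two parents, and "the number of clients in each condition is calculated to be 60".

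Under Condition 1: EFST Intervention, treatment starts with a workshop over two days, led by two therapists. Its size is given as "Each group consists of 6–16 parents, ideally both parents of a referred child". Six individual sessions follow. The same section puts 13 of the 19 treatment hours in the group.

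Under Condition 2: TAU, the treatment is non-manualised family therapy. Each family is seen separately by two therapists, who belong to a team that discusses its cases.

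The Therapists section says "Five qualified EFST therapists employed on the family team" deliver EFST. Of the other arm it says "Therapists in the TAU condition are all qualified mental health professionals employed at the" clinic's family team, with N = 12. It does not say whether the 12 include the five, or whether any therapist works in both arms.

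Under Data analyses, "Independent sample t-test will be performed on the SDQ" after every five clients, and collection may stop on strong evidence of a difference. Bayesian growth curve analysis is named for the same hypothesis, without its levels. Analyses are by intention to treat. The SDQ is the second outcome measure; the primary outcome is the K-SADS-PL diagnosis, rated present or not.

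**The concern.** This is a partially nested trial: one arm is treated in groups and the other is not. Families in the same workshop share leaders, group atmosphere and the experience of the other parents for about two-thirds of their treatment hours (13/19 = 0.68). If that makes their outcomes alike, 60 EFST families carry less information than 60 independent ones.

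An independent-sample t-test ignores this and reports too small a standard error. Understated uncertainty makes a false difference easier to declare, and also false equivalence, which is the hypothesised result. The stopping looks depend on the same test, so the error also reaches the decision to end recruitment.

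This is more than a detail left to an analysis plan. The article itself names a test whose key assumption conflicts with the delivery format it describes.

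**Working it through.** **The plan's own figure.** The plan gives no ICC or design effect, so there is no clustering figure to reproduce. The 60 per arm is stated thus: "With 80% power, an expected effect size of 0.4, and an anticipated 20% drop-out rate", "following a procedure described by Schönbrodt & Wagenmakers". A standard two-arm formula with two-sided 5% (assumed) gives 2 × (1.96 + 0.84)² / 0.4² ≈ 98.1, so 99 per arm before drop-out. The 60 is therefore not reproduced. That is a separate and larger issue, and 60 serves here only as an input.

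**Inputs from the document**
- 60 families per arm; with 20% drop-out, 60 × 0.8 = 48 completers.
- 6–16 parents per workshop: 3–8 families if both parents attend, up to 16 if one parent attends per family. For 60 families this means 60/16 = 3.75 to 60/3 = 20 workshops.
- Five EFST therapists: 60/5 = 12 families each, if each family had one individual therapist (assumed; the document does not say).

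**Assumed inputs**
- ICC of 0.01 to 0.10.
- A two-sided 5% level with critical value 1.96, for illustration only.

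**Formulas.** With m families per cluster, the EFST design effect is DE = 1 + (m − 1) × ICC. With equal arms, variances otherwise equal and clustering in EFST only, the ratio of true to naive standard error is R = √((1 + DE)/2). The actual two-sided error is 2 × (1 − Φ(1.96/R)).

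| m | ICC | DE | R | Actual error |
|---|---|---|---|---|
| 6 | 0.01 | 1.05 | 1.012 | 5.3% |
| 6 | 0.02 | 1.10 | 1.025 | 5.6% |
| 6 | 0.05 | 1.25 | 1.061 | 6.5% |
| 6 | 0.10 | 1.50 | 1.118 | 8.0% |
| 12 | 0.02 | 1.22 | 1.054 | 6.3% |
| 12 | 0.05 | 1.55 | 1.129 | 8.3% |
| 12 | 0.10 | 2.10 | 1.245 | 11.5% |
| 16 | 0.01 | 1.15 | 1.037 | 5.9% |

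Worked line: m = 6, ICC 0.10 gives DE = 1 + 5 × 0.10 = 1.50; R = √(2.50/2) = 1.118; 1.96/1.118 = 1.753; error 8.0%.

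**Sequential looks.** A simulation used a default-prior Bayes-factor t-test with looks every five per arm, a maximum of 48 per arm, no true difference and 1,500 runs. The chance of ever passing a Bayes factor of 10 for a difference was 1.5% with independent families. It was 2.5–7.7% with ICC 0.05–0.10 and 4–12 families per cluster. The prior and the threshold are assumptions.

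**Equivalence.** As an illustrative rule, require a 90% interval inside ±0.40. At 48 per arm the naive half-width is 1.645 × √(2/48) = 0.336. The chance of wrongly concluding equivalence at a true difference of 0.40 is 3.9% at DE 1, 4.7% at DE 1.35 and 5.9% at DE 2.10.

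**The case against.** **The growth curve may already handle it.** Its levels are not described, and an article commonly leaves random effects to the full analysis plan. This stands: the growth curve is unspecified, not wrong. It does not rescue the t-test or the stopping looks that rest on it.

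**Only a secondary outcome is affected.** True of the named test, since the primary outcome is the K-SADS-PL diagnosis. The same test nevertheless governs when data collection may stop.

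**The ICC is assumed, and so is the 5% level.** Both stand. With an ICC of 0.01 the standard error ratio stays at or below 1.04 even with 16 families per workshop. The 12-family cluster also needs one therapist per family, which is not stated.

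**A stronger reading: the contrast is diluted toward equivalence.** A reader might infer this because both arms are staffed from one team, TAU is non-manualised and discussed in team, and the department is one "which has offered EFST to more than one hundred families during 2021". The documents do not support it as fact. They do not say that the five EFST therapists treat TAU families or that TAU uses EFST techniques, and the 2021 remark describes department activity, not conduct in the trial. EFST is also distinct in format: a manual, a parents-only workshop and videotaped, supervised sessions. If 10–50% of a true 0.40 were lost (assumed), 0.36–0.20 would remain; if the arms are truly equal, there is nothing to dilute.

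**A richer model would be over-parameterised.** Separate effects for workshop, therapist, TAU therapist pair and parent within family ask too much of 120 families and perhaps four workshops. Excluding TAU families by who treated them would be a one-arm, post-randomisation exclusion at odds with the intention-to-treat statement. Both objections stand and limit the remedy.

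**Conclusion.** The concern holds for the SDQ t-test and the stopping rule built on it. The test assumes independence that the EFST delivery format gives good reason to doubt.

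The size is modest to material, not decisive. With 6 families per cluster and an assumed ICC of 0.02–0.10, the true standard error is 2–12% larger than the naive one, and a nominal 5% error becomes 5.6–8.0%. It reaches 6.3–11.5% if clusters of 12 apply. With an ICC of 0.01 it hardly matters. All of this rests on a positive ICC, clustering in EFST only, equal cluster sizes and a 5% level that the plan does not state.

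The error works in both directions, so it does not by itself favour equivalence. Contamination would favour equivalence if a true difference exists, but shared staffing only opens that route; it does not show that it is used.

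**What to change.** - Replace the t-test, at the final comparison and at every stopping look, with a partially nested model: a workshop random effect in the EFST arm only, arm-specific residual variance, and a weakly informative prior on the workshop variance.
- Use the same workshop term in the growth-curve comparison of the arms.
- Examine therapist in a sensitivity analysis instead of adding it to the main model.
- State whether therapists may work in both arms. Add therapist identity to the information on TAU that the protocol already plans to collect, and report any crossover descriptively. Keep all TAU families in the intention-to-treat comparison.

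Cost: a change of analysis wording and one field in an existing data collection; randomisation and treatment do not change. Intervals become slightly wider. With perhaps four to twenty workshops the cluster variance will be imprecise and will depend on its prior, most of all at early looks when only one or two workshops have run. Results under more than one prior should therefore be shown.
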